## Abstract

Bariatric surgery is the most efficacious treatment for obesity, though it is not free from complications. Preoperative conditioning has proved beneficial in various clinical contexts, but the evidence is scarce on the role of prehabilitation in bariatric surgery. We describe the protocol and pilot study of a randomized (ratio 1:1), parallel, controlled trial assessing the effect of a physical conditioning and respiratory muscle training programme, added to a standard 8-week group intervention based on therapeutical education and cognitive-behavioural therapy, in patients awaiting bariatric surgery. The primary outcome is preoperative weight-loss. Secondary outcomes include associated comorbidity, eating behaviour, physical activity, quality of life, and short-term postoperative complications. A pilot sample of 15 participants has been randomized to the intervention or control groups and their baseline features and results are described. Only 5 patients completed the group programme and returned for assessment. Measures to improve adherence will be implemented and once the COVID-19 pandemic allows, the clinical trial will start. This is the first randomized, clinical trial assessing the effect of physical and respiratory prehabilitation, added to standard group education and cognitive-behavioural intervention in obese patients on the waiting list for bariatric surgery. Clinical Trial Registration: NCT0404636.

## 1. Introduction

Obesity is a global public health issue, associated with high morbimortality and health costs. Bariatric surgery is the most effective treatment for obesity and its complications [1,2,3,4,5,6]. The remission of type 2 diabetes is seen in 23–60% of patients, depending on the type of procedure, as well as the severity and duration of the disease [7,8]. Bariatric surgery can also prevent 82% of new-onset diabetes [1], improve glycaemic control [9,10], and reduce diabetes complications more effectively that non-surgical treatments [4,5,9,10]. Hypertension improves within the first postoperative month and this improvement is long-lasting [2,11] and the need for lipid-lowering drugs and continuous positive air pressure therapy during sleep are also reduced by 82% and 70–90%, respectively [3]. Furthermore, after bariatric surgery, obese patients have lower cardiovascular, cancer, and all-cause mortality than unoperated peers [5,8,12]. Nevertheless, although surgery is the most effective weight-loss measure, obese people are at high risk for surgical complications. Thus, success depends not only on the chosen surgical procedure but also on the patient’s preparedness for surgery. Indeed, psychosocial-behavioural assessment, as well as a multidisciplinary intervention on diet, physical activity, and behaviour change are recommended [13].

Preoperative weight loss is associated with a reduction in surgical complications, intervention complexity, and hospital length of stay [6,14,15,16,17,18,19]. Tested interventions include lifestyle changes, nutritional education, physical activity, cognitive-behavioural therapy, and pharmacological treatment. In a systematic review and meta-analysis, pre-operative weight loss appeared to be associated with greater post-operative weight loss [20], an effect which is especially evident in patients with a BMI above 45 kg/m^2^ [21].

In 2016, the Enhanced Recovery After Surgery (ERAS) Society published its guidelines for bariatric surgery [22], which included preoperative weight-loss, smoking, and alcohol cessation and preoperative instructions for increased adherence, quick recovery and shorter hospital stay. In addition, the guidelines now include “prehabilitation”, preoperative physical conditioning to increase functional capacity and prepare the patient for the metabolic stress associated with surgery. In abdominal oncological surgery, orthopaedic and cardiopulmonary surgery, prehabilitation has led to improved postoperative respiratory and muscular functional capacity [23,24,25,26,27,28,29,30,31,32,33,34,35,36,37]. There is less evidence of harder outcomes, such as complications and length of hospital stay [38]. In obese patients, preoperative physical activity is associated with a reduction in cardiometabolic risk, premature mortality, and postoperative complications [39,40], but specific interventions before bariatric surgery are scarce. Hence, the recommendation of prehabilitation by ERAS in this context is not strong, though it is described as promising [22]. International guidelines currently recommend specialised dietary advice by a dietitian trained in long-term behaviour changes, both for the preoperative and the postoperative periods [13,41]. A few studies have shown improved postoperative pulmonary capacity and resistance following prehabilitation with the training of inspiratory muscles [42,43,44], which might lead to fewer respiratory complications.

In the present report, we describe the study protocol and the pilot survey for a randomized controlled trial assessing the effect of physical conditioning and inspiratory muscle training (prehabilitation) in people awaiting bariatric surgery, on preoperative weight-loss, comorbidities, and postoperative complications.

## 2. Materials and Methods

### 2.1. Study Design

This is a randomized, parallel, controlled trial assessing the effects of a 16-week programme including physical activity and a minimal respiratory physiotherapeutic intervention on pre-surgical weight-loss in patients awaiting bariatric surgery.

Eligible patients are randomized to one of two treatment groups: a standard, multidisciplinary treatment (control), consisting of an education programme and cognitive-behavioural intervention or the same treatment in addition to physical activity and respiratory muscle training (intervention, i.e., prehabilitation).

Written informed consent is obtained from all participants, and the trial was conducted in accordance with the principles stated in the Declaration of Helsinki and the European Medicines Agency Good Clinical Practice Homogenized Guidelines. The study protocol was approved by the provincial Ethics Committee and registered at ClinicalTrials.gov (NCT04046367) on 6 August 2019.

### 2.2. Study Population

All patients on the waiting list for bariatric surgery with obesity grade III–IV selected according to the 2016 Position Statement of the Spanish Society for the Study of Obesity [45], expected to be operated on at least 4 months after inclusion, are potentially eligible and are approached by phone. Those who agree, are scheduled for an appointment at the hospital, where more detail is given about the trial. Participants sign written informed consent before inclusion. The only exclusion criteria are those limiting participation in the programme (according to the investigators’ assessment), such as timing difficulties or linguistic barriers. Figure 1 shows a flowchart of the study.

### 2.3. Randomization and Allocation Masking

Participants are assigned to their treatment group (ratio 1:1) following a computer-generated random sequence. The latter is generated by a lab technician otherwise not involved in the trial. It is transferred to individual cards, which are inserted into opaque, sealed, consecutively numbered envelopes. When the participant signs the consent form and eligibility is confirmed, the first sealed envelope is opened to reveal the treatment group, and the patient is scheduled for the baseline assessment tests and the eight fortnightly sessions.

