### 2.4. Intervention Masking

Participants are informed that two different group programmes are compared, but no detail is given about the difference between them. Most outcomes are not expected to be affected by the investigators’ knowledge of the treatment arm. An assessment of functional capacity is performed, whenever possible, by explorers unaware of the participant’s assigned treatment.

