### 2.7. Outcomes

The primary outcome is the change in body weight between the start of the programme and the time of surgery.

Secondary outcomes include: changes in body composition, comorbidities, changes in eating behaviours, health-related quality of life, functional capacity, length of hospital stay after surgery and short-term complications of surgery.

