### 2.9. Body Composition

Body composition is assessed at the baseline visit. Weight is assessed with a calibrated bioimpedance (*Tanita BC 420 MA III*, Tokyo, Japan) to the nearest 0.1 kg, and height, using a stadiometer to the nearest 0.5 cm, without shoes and with light clothing. Body Mass Index (BMI) is then calculated as weight (in kg) divided by height (in meters)^2^. Body composition is analyzed through Vectorial Bioimpedance by tetrapolar impedance plethysmography using an electric alternating current flux of 400 µA at an operating single sinusoidal frequency of 50 kHz (*Nutrilab™*, Akern, Firenze, Italy in resting conditions. Standard whole-body measurements are performed according to the manufacturer’s guidelines on the right side of the body with the subjects in supine position with their arms and legs abducted, and the skin cleaned to ensure good contact. The thighs are checked not to be in contact with each other and the arms not to be touching the sides of the body. Electrodes are placed on a line between the radial and ulnar styloid processes on the dorsum of the wrist and on a line between the medial and lateral malleoli on the dorsum of the ipsilateral foot, overlying the head of the third metacarpal on the dorsum of the hand and the third metatarsal on the dorsum of the foot. Total body water, fat-free mass, fat-free mass percentage, fat mass, fat mass percentage and body cell mass are determined according to the formulas of Kotler et al. [48], and bioelectrical parameters of resistance, reactance, and phase angle are registered.

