## 3. Results

Participants in the pilot study had their first visit between 8 August 2019 and 13 September 2019, and the interventions took place between October 2019 and January 2020. 

Out of the 51 patients on the waiting list, expected to be operated on at least 4 months after recruitment, 19 accepted to participate. The main reasons given for declining were participation in preoperative groups in another centre (on a different island), distance to the training site and schedule problems, mainly due to working hours. None of the patients refused to participate or was excluded due to linguistic barriers. A total of 15 (14 women) attended the first visit and were randomized. Their mean age was 40.0 ± 10.0 years, baseline BMI, 46.7 ± 5.9 kg/m^2^, and waist circumference 134.2 ± 12.0 cm. The most frequent complications of obesity were OSA (54%), osteoarticular disorders (40%), asthma (33.3%), hypertension (33.3%), infertility (35.7%), chronic venous insufficiency (28.6%), diabetes (26.7%), and dyslipidaemia (26.7%). Seven patients were randomized to the intervention group and 8 to the control group. Their baseline features are displayed in Table 2.

The first eight sessions took place between October 2019 and January 2020. Three participants dropped out before even starting the intervention (one travelled abroad, another one said the timing of the sessions was inconvenient, and the third did not give a specific reason). The rest attended between one and six sessions. Only five participants completed follow-up, three in the intervention and two in the control group. Of the ten patients not completing the programme, seven interrupted it due to early surgery. Unlike what was initially planned, because of the low attendance at the sessions, we decided to merge both treatment groups from session 2, since group intervention was not possible otherwise. The control group left after the standard session finished, whereas the intervention group joined the physiotherapist team thereafter.

The five participants completing the follow-up lost an average of 0.54 ± 5.2 kg (Intervention group +1.6 ± 4.3 kg; Control group −3.8 ± 5.7 kg) and the final BMI was 48.1 ± 7.6 kg/m^2^ (Intervention Group 45 ± 7.3 kg/m^2^; Control group 52.69 ± 10.6 kg/m^2^). Given the small sample size, no statistical analysis was performed and no conclusions can be drawn.

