**Figure 3 nutrients-13-02903-f003:**
[figure not shown]
Inspiratory valve used in the training programme.

**Table 1 nutrients-13-02903-t001:** Programme contents.

Session	Description	Contents
Session 1	Welcome and introduction	Introduction Questionnaires completion Group dynamics activity
	Medical aspects 1 (Endocrinologist)	Obesity and its complications Treatment: drugs, intragastric baloon How to prepare for surgery: healthy lifestyle, weight-loss, cardiovascular risk factors. Evidence Bariatric surgery: procedures. Benefits and risks. What to expect from surgery Physical activity. How to monitor
Session 2	Nutrition 1 (Dietician)	Food groups The Mediterranean diet as example of a healthy diet. Portion size Calories
Session 3	Psychoeducation 1 (Psychologist)	I am not fat. Differences between trait and state Weight regain and how to deal with it. The importance of cognitive-behavioural changes Personality and food Behavioural strategies with food: the importance of how and what to eat How to create a habit. Setting realistic goals
Session 4	Nutrition 2 (Dietician)	How to do the shopping Reading food labels
Session 5	Psychoeducation 2 (Psychologist)	Cognitive restructuring: identifying, analysing and modifying negative and irrational thoughts associated with eating behaviours How to say NO Self-control and travelling, celebrations, and eating out
Session 6	Nutrition 3 (Dietician)	Unnecessary foods Sweeteners Miraculous diets Myths
Session 7	Psychoeducation 3 (Psychologist)	Self-esteem and self-trust Strategies to reduce stress and anxiety Progressive relaxation technique
Session 8	Medical aspects 2 (Endocrinologist)	Postoperative diet. Protein sources. How to enrich food. Vitamin supplementation. Postoperative follow-up Weight regain When to go to the emergency room Changes in drug treatments after surgery. Long-term complications. Frequent problems after surgery: heartburn, reflux, dumping, diarrhoea. Skin flaps Pregnancy

**Table 2 nutrients-13-02903-t002:** Baseline characteristics of the pilot study population, according to the assigned treatment group ^1^.

	Intervention (*n*= 7)	Control (*n*= 8)
Age (years)	38 ± 10	41 ±10
Sex (*n*) Women/Men	7/0	7/1
Weight (kg)	112.9 ±19.5	135.9 ±23.2
BMI (kg/m^2^)	44.7 ± 4.5	48.5 ± 6.7
Waist circumference (cm)	130.4 ± 12.1	138.0 ± 11.4
FM (%)	47.7 ± 4.1	52.4 ± 3.8
PA (°)	6.6 ± 0.6	6.0 ± 0.6
6MWD (m)	447.1 ± 83.5	433.5 ± 37.4
6MWD (%)	86.1 ± 16.1	90.8 ± 12.5
HGS Right Hand (kg)	24.0 ± 7.7	29.7 ± 9.1

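### Allocation is revealed before the baseline tests and weeks ahead of the first session, which leaves effort-dependent and self-reported baselines incompletely masked and turns pre-start withdrawals into randomised losses

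*Protocol article*

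**What the plan says.** **Order of steps.** Section 2.3 (Randomization and Allocation Masking) acts once consent is signed and eligibility is confirmed. At that point "the first sealed envelope is opened to reveal the treatment group, and the patient is scheduled for the baseline assessment tests" and for the eight fortnightly sessions.

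**Masking.** Section 2.4 says of participants: "Participants are informed that two different group programmes are compared, but no detail is given about the difference between them". For assessors it says: "An assessment of functional capacity is performed, whenever possible, by explorers unaware of" the assigned arm. For the rest it accepts that the arm may be known: "Most outcomes are not expected to be affected by the investigators" knowing the arm.

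**Outcomes.** Section 2.7: "The primary outcome is the change in body weight between the start of the programme and the time of surgery". Functional capacity, quality of life and eating behaviour are among the secondary outcomes. On the primary measurement, Section 2.9 says: "Weight is assessed with a calibrated bioimpedance" device, to the nearest 0.1 kg.

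**Questionnaires.** Section 2.10 has them self-completed ahead of the first group session. Table 1 lists "Questionnaires completion" among the contents of Session 1.

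**Pilot.** Section 3 (Results) dates the first visits from 8 August to 13 September 2019 and the sessions from October 2019. Fifteen patients were randomised, and "Three participants dropped out before even starting the intervention".

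**Analysis.** Section 2.15 plans 80 participants with no loss to follow-up, analysis by intention to treat, and last observation carried forward (LOCF) for missing values.

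**The concern.** Two separate things follow from opening the envelope early.

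The first concerns measurement. A baseline taken after allocation is protected only by masking, and here masking is partial. The arms are scheduled in alternate weeks (Section 2.5), so anyone who opens envelopes or books sessions can know the arm. The six-minute walk, handgrip and maximal inspiratory pressure depend on the patient's effort and the tester's conduct. If a tester who knows the arm handles the baseline differently, the between-arm difference in change is distorted, and nothing in the data would show it.

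The second concerns who counts as randomised. The longer the gap between envelope and first session, the more patients drop out after allocation without starting. They belong to the intention-to-treat set. Those without a later weight contribute a change of zero, which pulls the estimated difference towards zero in a trial sized for complete follow-up.

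**Working it through.** **1. Which baselines are exposed**

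| Baseline measure | Protection stated | Exposure to knowledge of the arm |
|---|---|---|
| Six-minute walk, handgrip, maximal inspiratory pressure (Section 2.11) | Unaware tester for functional capacity where feasible (Section 2.4) | Real: effort-dependent, masking not assured |
| Questionnaires (Section 2.10, Table 1) | Participants not told how the arms differ | Smaller: self-completed, but after allocation |
| Weight (Section 2.9) | None stated, but read from a calibrated device | Low: no evident route to the reading |

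Sections 2.10 and Table 1 differ on whether the questionnaires precede Session 1 or form part of it. On either timing they follow the envelope.

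**2. Gap between allocation and start in the pilot**

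Assumption: allocation took place at the first visit, as Section 2.3 implies. The exact day in October is not given, so 1 October is the earliest possible start.
- Last first visit: 13 September to 1 October = 18 days.
- Earliest first visit: 8 August to 1 October = 54 days.

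The gap was therefore at least about two and a half weeks for everyone, and longer for most if visits were spread over the period.

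**3. Pre-start loss**

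3/15 = 20%. The exact (Clopper-Pearson) 95% interval is 4.3% to 48.1%.

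**4. The plan's own figure**

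Inputs from Section 2.15: 40 per arm, SD 11 kg, two-sided 5%, no loss. The normal approximation is: detectable difference = (1.96 + z for power) × 11 × √(2/40).
- 80% power: 6.9 kg (two-sample t-test: 7.0 kg).
- 90% power: 8.0 kg (t-test: 8.1 kg).

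The figures 7 and 8 kg are reproduced, but with 7 kg belonging to 80% and 8 kg to 90%, the reverse of the printed pairing. That is a separate matter. For 7 kg the t-test power at 40 per arm is 0.80.

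**5. Illustration of dilution under the stated analysis rules**

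Assumptions: a fraction d of each arm leaves before starting, has no later weight and is carried forward at zero change. The true difference among starters is 7 kg. All 40 per arm stay in the analysis.

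Diluted difference = 7 × (1 − d).

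The SD is uncertain, so two cases are shown:
- (a) SD stays at 11 kg.
- (b) SD is 11 kg among starters and the zeros are mixed in: variance per arm = (1 − d) × 121 + d(1 − d) × mean². The control mean is taken as 0 and the intervention mean as 7 kg lost.

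For d = 0.20 in case (b): intervention 96.8 + 0.16 × 49 = 104.6; control 96.8; pooled SD = √100.7 = 10.0 kg.

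| d | Diluted difference | Power, case (a) | Power, case (b) |
|---|---|---|---|
| 0 | 7.0 kg | 0.80 | 0.80 |
| 4.3% | 6.7 kg | 0.77 | 0.78 |
| 20% | 5.6 kg | 0.61 | 0.69 |
| 48.1% | 3.6 kg | 0.31 | 0.49 |

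**The case against.** **Masking is partial, not absent.** Participants do not know what distinguishes the programmes. Section 2.6 gives both arms the same two-hour session before the intervention part begins, and devices are handed out only when the first session ends. A patient who fills in questionnaires during Session 1 has therefore not yet seen the difference. This stands, and it is why the questionnaires are put below the effort-dependent tests.

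**The primary outcome is hardly touched by measurement bias.** This also stands. A reader might infer that every change-from-baseline outcome, weight included, is biased by the order of steps. The article does not support that. Weight comes from a calibrated device, and Table 2 reports it for 7 and 8 patients with no missing entries noted.

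**Missing baseline items are not evidence against the order.** A reader might take the gaps in Table 2 as harm from early allocation. The unavailable counts are nearly equal between arms (IPAQ 2 and 2, HADS 2 and 2, MEDAS 2 and 1), and nothing ties them to allocation. The sleep apnoea percentages cannot settle how many were tested. Those in Table 2 imply 4 and 6 patients, hence 6/10 = 60%, whereas the Results give 54%.

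**Attrition is mostly another problem.** Seven of the ten pilot non-completers stopped because of early surgery, which this order does not cause. Taking baseline first would not by itself have removed the three early leavers, since Table 2 suggests that at least some baseline data exist for all 15. Only allocation close to the first session might have. This stands and shapes the fix.

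**Deleting the early leavers and recomputing power with fewer patients would be wrong.** Section 2.15 keeps them in, so the relevant effect is dilution. A drop-out who is later operated on and weighed would not need imputation, and the dilution would then be smaller than shown.

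**Conclusion.** The point holds as a modest design weakness. The order in Section 2.3 is explicit, and Section 2.4 does not fully compensate for it. The baselines of the six-minute walk, handgrip and maximal inspiratory pressure are not assured against knowledge of the arm. Those of the questionnaires are so to a lesser degree, and baseline weight is largely safe. No size can be put on the measurement bias from the article, and there is no evidence that it occurred in the pilot.

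The second consequence has a rough size. Pre-start loss was 3 of 15, with an interval so wide (4% to 48%) that 20% is only a marker. If it recurred in both arms with no later weights, the expected difference would fall by a fifth, from 7 to 5.6 kg, with power of about 0.61 to 0.69 depending on the SD, against 0.80 with no loss. These powers are illustrations and rest on the assumptions given with them. They describe pre-start loss, only part of which later allocation could prevent. The change is worth making because it is cheap and the main trial had not begun when the article was written.

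**What to change.** Rewrite Section 2.3 so that the sequence is:
1. Consent and confirmed eligibility.
2. Baseline assessments and questionnaires, all done before allocation. Reconcile Section 2.10 with Session 1 of Table 1 by moving the questionnaires to the baseline visit.
3. Reconfirmation that the patient is still available for the coming sessions. Section 2.6 of the pilot programme need not change, and Section 2.2 already treats timing difficulties as a reason for exclusion.
4. Envelope opened, shortly before the first session of that cohort.

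Do not make complete data on every baseline item a condition of randomisation. The battery includes home polygraphy, full lung function and arterial gases, and recruitment was already hard (19 of 51 accepted in the pilot). Such a rule would exclude patients for no gain.

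The cost is a reordering of existing steps, with no extra visit or staff. The downside is that patients learn later which week their group meets. Section 4 (Discussion) already foresees protocol changes going to the Ethics Committee, so this one can go with them. It does not replace an allowance for loss in the sample size, nor the coordination with surgery that the authors plan.
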